### Relevant concomitant care permitted or prohibited during the trial {11d}

Ongoing or planned amblyopia treatment (except spectacles) was prohibited. Ongoing or planned use of medications that may affect vision (except dilating eye drops, e.g., atropine used for optometry examinations) was prohibited.

### Provisions for post-trial care {30}

In case of any probable adverse event, the study treatment will cease and appropriate medical protection will be provided by the research team for compensating probable harm.

### Outcomes {12}

#### Primary outcomes

The total effective proportion of amblyopia treatment at week 13. The effective amblyopia treatment is defined as at least 0.2 logMAR improvement of the BCVA at distance in the AE from baseline after treatment, measured with cycloplegic refraction using electronic ETDRS chart. The effective proportion will be calculated for each group.

Effective proportion (%) = Total number of patients meeting the criteria for effective amblyopia treatment/Total number of patients receiving amblyopia treatment in the analysis set × 100.

#### Secondary outcomes

Secondary outcomes included the mean change from baseline to week 13 in the habitual-corrected visual acuity at distance in the AE, the contrast sensitivity in each eye, the stereoacuity at near and distance, the interocular suppression measured by worth-4 dot at near and distance, and the interocular suppression measured by Bagolini striated lens at near and distance, the treatment adherence and safety reports. Additional outcomes included all the measures at week 2, 4, and 9 for the analysis of within-person changes over time.

### Participant timeline {13}

The schematic of the study procedure is displayed in Fig. 2.

**Fig. 2 Fig2:**
[figure not shown]
Schematic of the study procedure

#### Screening and eligibility assessment

Potential participants are identified from patients coming to the ophthalmology department of the participant centers. Based on the patients' informed consent, medical history and ophthalmic examinations will be evaluated by the investigators for the eligibility screening. Medical history includes a history of ocular diseases, amblyopia treatment and other significant diseases (such as tumor, hypertension, diabetes, heart disease, and epilepsy), a history of ocular surgery, and a history of other major surgeries within the past year. In addition, patients who can not achieve binocular fusion (e.g., uncorrected strabismus) when using AR binocular training devices will be excluded. Ophthalmic examinations are performed for amblyopia diagnosis and patient screening, including the anterior segment examination, fundus photography and optical coherence tomography, prism and alternate cover test, ocular motility, refractive error (cycloplegic refraction in aged ≤ 14), best-corrected visual acuity at near (for presbyopes) and distance, interocular suppression, and stereoacuity. Participants were required to have stable visual acuity before enrollment, defined as wearing the appropriate and same glasses for at least 12 weeks until five or fewer letters change in 2 consecutive visual acuity measurements in the AE (at least 4 weeks apart).

#### Baseline and follow-up assessments

The evaluation schedule of the study is displayed in Table 1. All the measurements are finished by the masked examiners at each visit.

**Table 1 Tab1:** Summary of trial design

Item\schedule	Study duration					
	Enrollment screening and baseline measurement	Randomization	Treatment period			
	Visit 1 Day − 7 ~ Day 0	Visit 2 Day 0	Visit 3 2 weeks ± 3 days	Visit 4 4 weeks ± 3 days	Visit 5 9 weeks ± 3 days	Visit 6 13 weeks ± 3 days
Allocation		X				
Anterior segment	X					X
Fundus check	X					X
Prism and alternate cover test	X					X
Ocular motility	X					X
Worth 4-dot	X		X	X	X	X
Bagolini striated lens	X		X	X	X	X
Randot Stereotest	X		X	X	X	X
Visual acuity	X		X	X	X	X
Contrast sensitivity	X		X	X	X	X
Axial length	X		X	X	X	X
Refraction	X		X	X	X	X
Adherence	X		X	X	X	X
Adverse events	X		X	X	X	X

Visual acuity in each eye will be measured with the ETDRS chart with Tumbling E target at 4 m (uncorrected visual acuity and habitual-corrected visual acuity) and the electronic ETDRS with Tumbling E target at 2.5 m (BCVA). Contrast sensitivity in each eye will be tested at 2.5 m with the CSV-1000® instrument (VectorVision, Greenville, OH, USA) in a darkroom, for 4 frequencies in cycles per degree (cpd), including 3, 6, 12, and 18 cpd. Interocular suppression will be evaluated by the Worth-4 dot test and Bagolini striated lens test at 33 cm and 6 m. Stereoacuity will be tested by the Randot stereotest (Stereo Optical Co., Inc., Chicago, IL) at 40 cm and 3 m. The anterior segment examination, fundus check (fundus photography and optical coherence tomography), binocular alignment (prism and alternate cover test) and ocular motility evaluation (nine cardinal positions of gaze for function evaluation of extraocular muscles) will be performed only at the baseline and final visit. Other evaluations including refractive error (cycloplegic refraction in aged ≤ 14), axial length, adherence, and adverse events will be performed at each visit.$$\mathrm{Adherence}\;(\%)=(\mathrm{Completed}\;\mathrm{treatment}\;\mathrm{days}/\mathrm{Scheduled}\;\mathrm{treatment}\;\mathrm{days})\times100$$

The patient adherence is graded as "excellent", "good", "fair", and "poor" when ranging between 76-100%, 51-75%, 26-50%, and 25% or below, respectively. Moreover, at the final visit after completing the treatment, both investigators and patients in the AR training group will evaluate the satisfaction with the software's functions and ease of use.

Safety reports assessment of the types (adverse event, serious adverse event, device deficiency), incidence rate (%), and frequency (number of events) of adverse events and device-related adverse events, serious adverse events and device-related adverse events, and device deficiency occurring during the clinical trial.

### Sample size {14}

According to the requirements of the Good Clinical Practice for Medical Devices ([2022] No. 28) and the Guidance for the Design of Medical Device Clinical Trials, sample size estimation will be performed referring to the clinical study results of comparable medical devices of the investigational medical device and clinical expert opinions.

In this study, the sample size will be calculated based on the primary endpoint, namely the total effective proportion at 13 weeks, using the superiority design. Considering the treatment effects are strongly age-dependent, the participants are divided into 2 groups based on ages: Subgroup I (aged 5 to under 18 years) and Subgroup II (aged 18 to under 55 years).

Subgroup I: Based on clinical expert opinions and preliminary study results (unpublished data), the anticipated effective proportion at 13 weeks of the intervention group will be 75%, while that of the control group, based on previous literatures [10, 21, 22] and clinical expert opinions, will be 40%. With a superiority margin of 0 and a 1:1 ratio of intervention group to control group, the sample size required for each group is 28, as calculated using the PASS 2022 software, at the 5% significance level (two-sided) with 80% power. Considering the 15% dropout proportion during the study, 33 patients will be included in the intervention group and the control group, respectively, in patients aged 5 to under 18 years.

Subgroup II: Based on expert opinions and preliminary study results (unpublished data), the anticipated effective proportion at 13 weeks of the intervention group will be 60%, while that of the control group, based on previous literature [23, 24] and clinical expert opinions, will be 20%. With a superiority margin of 0 and 1:1 ratio of intervention group to control group, the sample size required for each group is 20 as calculated using the PASS 2022 software, at the 5% significance level (two-sided) with 80% power. Considering the 15% dropout proportion during the study, 24 patients will be included in the intervention group and the control group, respectively, in patients aged 18 to under 55 years.

In summary, this clinical study is expected to enroll a total of 114 participants, with 57 patients (33 patients in Subgroup I and 24 patients in Subgroup II) in each group. The formula for calculation of sample size is shown as follows:$$n_{T} = n_{C} = \frac{{\left( {Z_{1 - \alpha /2} + Z_{1 - \beta } } \right)^{2} \left[ {P_{C} \left( {1 - P_{C} } \right) + P_{T} \left( {1 - P_{T} } \right)} \right]}}{{\left( {\left| D \right| - \Delta } \right)^{2} }}$$

*P*_*T*_ and *P*_*C*_ are the expected event proportions of the intervention group and control group, respectively;$$\left| D \right|$$ is the absolute value of the difference between the expected proportions of the two $$\left| {P_{T} - P_{C} } \right|$$; Δ is the superiority margin.

### Recruitment {15}

Patients were recruited from the outpatient of the participating centers, where there were considerable ophthalmic patients and professional conditions for amblyopia evaluation and diagnosis.

## Assignment of interventions: allocation

### Sequence generation {16a}

With age (5– < 18 years old, 18– < 55 years old) as a stratified factor, patients will be assigned sequentially into “intervention group” and “positive control group,” according to the randomization sequence generated by the statistician using the PROC PLAN procedure in SAS at a 1:1 ratio.

### Concealment mechanism {16b}

The treatment allocation will be done using a web-based randomization system Clinflash Cloud (https://cloud.clinflash.com) and undertaken by the investigator. Physicians conducting examinations and data analysts were masked to group assignment. Patient masking is not possible in this study; therefore, no code breaking procedures were required.

### Implementation {16c}

With age (≥ 18 years old, < 18 years old) as the stratified indicator, all eligible patients who had signed the written informed consent after a detailed explanation about the trial were randomly divided into two groups respectively named “AR training group” and “positive control group,” at a 1:1 ratio according to the randomization sequence generated by the statistician.

## Assignment of interventions: blinding

### Who will be blinded {17a}

Physicians who conduct follow-up examinations and data analysts cannot know the grouping of patients, physicians receive professional training about visual function evaluation involved in this trial, and staff outside the research team input the data into the Electronic Data Capture (EDC) system. The statisticians cannot know the grouping during data analysis.

### Procedure for unblinding if needed {17b}

Participants cannot be blinded due to significant differences in interventions in this trial. No procedure for unblinding will be needed as all data analyses are performed after the trial is closed.

## Data collection and management

### Plans for assessment and collection of outcomes {18a}

Demographic data, present and past history on amblyopia diagnosis and treatment, present and past history on medication usage and surgery, systemic and mental diseases will be recorded at the assessment of eligibility. Multiple follow-up assessments included visual acuity, contrast sensitivity, binocular depression, and stereoacuity. Follow-up schedules will be the same for both groups. Baseline data and the 13-week visit included follow-up assessments mentioned above and other assessments including anterior segment examination, axial length, fundus photography, and optical coherence tomography, prism and alternate cover test, and ocular motility. The research schedule is shown in Table 1.

### Plans to promote participant retention and complete follow-up {18b}

A comprehensive informed consent process will be conducted to ensure participants fully understand the trial objectives, procedures, and follow-up requirements. The importance of completing the whole follow-up will be emphasized. We will provide participants with a 13-week follow-up schedule and encourage them to visit the clinic on the assigned date. Two days before the follow-up date, the Clinical Research Coordinator (CRC) will proactively remind the patients via phone. Visit dates are negotiated with participants within ± 3 days of the protocol-specified target window to balance scientific rigor and logistical feasibility. A final follow-up assessment, identical in content to the originally scheduled evaluation for that time point, will be conducted prior to therapy cessation if feasible.

### Data management {19}

The Internet-based data management system, the EDC system, was used for data entry, coding, security, and storage. This study will be participant to confidentiality agreements with staff, the data manager (DM), who manages EDC data and shall not modify or delete existing data without authorization. Unauthorized personnel cannot access EDC systems. The DM will design case report forms (CRFs) aligned with the study protocol and implement an EDC system for centralized data management. A data management plan made by the DM will govern all data handling procedures. A Data Validation Plan (DVP) will be developed pre-database activation, specifying system-generated automated queries and manual verification scopes. Manual verification will be carried out in schedule according to the DVP. A pre-lock review will be conducted to validate database completeness and accuracy prior to database lock.

Paper-based CRFs will be used for initial data collection. On the day of each follow-up visit, the PI will review and sign off on paper records to confirm validity before same-day EDC entry, and the CRC will input the data into the EDC system. Original paper documents will be archived securely. The Clinical Research Associate (CRA) will check the source data to ensure consistency with the contents on the electronic CRFs. All EDC data will be exported, encrypted, and archived on read-only optical discs for permanent retention post trial, complying with the Good Clinical Practice (GCP) and regulatory requirements.

### Confidentiality {27}

Patients and researchers are required to sign a confidentiality agreement to ensure that the data were restricted to the use for this project, to ensure the privacy and security of patient data, and to promise that the collected patient data will not be used for any other purpose without written permission.

### Plans for collection, laboratory evaluation and storage of biological specimens for genetic or molecular analysis in this trial/future use {33}

Not applicable.

## Statistical methods

### Statistical methods for primary and secondary outcomes {20a}

The normal quantitative variables will be described as the mean and standard deviation (SD), and other quantitative variables will be described using the median and interquartile range. Categorical variables are described as the number of cases and the percentage of each category. Independent-sample T test or Wilcoxon rank-sum test will be used for the comparison between groups of quantitative variables based on the data distribution characteristics, and chi-square test or exact probability test will be used for categorical variables.

Statistical analysis will be performed using the SAS 9.4 (or above). Unless specified, all statistical tests will be two-sided at the 5% significance level, and the difference is considered statistically significant when the p value is ≤ 0.05. The analysis will be performed on an intention-to-treat and also per-protocol approaches. No interim analyses are planned.

#### Analysis of primary endpoint

For the evaluation of the primary efficacy endpoint, the effective propotions (Wilson 95% CIs) and the between-group difference in effective proportions (Newcombe 95% CIs) at 13 weeks within Subgroups I and II are calculated. If the lower limit of the 95% CIs for the between-group difference in effective proportions within Subgroups I and II are > 0, then superiority is established. Primary analysis will calculate clinical response rates (Wilson 95% CIs) and rate differences (Newcombe 95% CIs) for treatment vs. control arms in Groups I/II at Week 13. Cochran-Mantel–Haenszel (CMH) analysis stratified by center will provide MH-adjusted proportion differences with 95% CIs for between-group comparisons. For the primary efficacy endpoint, results based on both the full analysis set (FAS) and per protocol set (PPS) are provided.

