### Methods in analysis to handle protocol non-adherence and any statistical methods to handle missing data {20c}

In accordance with the principle of ITT analysis, we will analyze the results of the primary outcome by participant randomization, regardless of patients' adherence to the intervention. The worst-case imputation method will be used to handle missing data for primary efficacy data.

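### The 80% power stated for each age subgroup comes from a Wald-type formula; under the Newcombe rule that decides superiority it is about 75% to 78%

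*Protocol article*

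**What the plan says.** In Sample size {14}, each age subgroup is sized separately, with a superiority margin of 0 and 1:1 allocation, "at the 5% significance level (two-sided) with 80% power". For Subgroup I (under 18) the assumed response rates are 75% and 40%, and "the sample size required for each group is 28, as calculated using the PASS 2022 software". For Subgroup II (18 and over) they are 60% and 20%, and the size is 20 per arm. Allowing for 15% dropout raises these to 33 and 24 per arm, 114 patients in all. The section prints its equation ("The formula for calculation of sample size is shown as follows"); the variance term is PC(1-PC) + PT(1-PT), the unpooled form.

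In Analysis of primary endpoint, the plan calculates "the between-group difference in effective proportions (Newcombe 95% CIs" within each subgroup, and superiority is established if the lower limit is above 0. A Cochran-Mantel-Haenszel analysis stratified by center gives a further adjusted estimate, but the superiority sentence is tied to the within-subgroup intervals. Section {20c} adds: "The worst-case imputation method will be used to handle missing data for primary efficacy data".

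**The concern.** A power figure belongs to a particular decision rule. The sizing equation corresponds to a Wald interval for the difference. The Newcombe interval is built from the two Wilson intervals and gives a different lower limit in small samples. With 20 to 28 patients per arm, some plausible results pass one rule and fail the other. If the Newcombe rule is the stricter, the stated 80% describes an analysis that will not be run, and readers are told of a slightly better chance of success in each subgroup than the plan gives them. The point concerns each subgroup on its own and does not depend on how the two results are combined.

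**Working it through.** **Inputs.** Sample size {14}: rates 75% v 40% and 60% v 20%; 28 and 20 evaluable per arm; 33 and 24 randomised per arm; 15% dropout; two-sided 5%; margin 0. Analysis of primary endpoint: Newcombe 95% lower limit > 0.

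**1. Reproduce the plan's figures.** n = (1.960 + 0.842)² × [PC(1-PC) + PT(1-PT)] / (PT-PC)², where (1.960 + 0.842)² = 7.849.
- Subgroup I: 7.849 × (0.2400 + 0.1875) / 0.35² = 27.39, so 28; 28/0.85 = 32.9, so 33.
- Subgroup II: 7.849 × (0.16 + 0.24) / 0.40² = 19.62, so 20; 20/0.85 = 23.5, so 24.

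All four figures reproduce. A pooled-variance formula gives 31 and 23, and a continuity-corrected one 36 and 28, so of these only the unpooled form returns the stated sizes.

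**2. Show that the two rules can disagree.** Take 12/20 v 6/20, a difference of 0.30.
- Wald lower limit: 0.30 - 1.96 × √(0.24/20 + 0.21/20) = 0.30 - 1.96 × 0.15 = +0.006, a success.
- Newcombe lower limit: the Wilson lower limit for 12/20 is 0.387 and the Wilson upper limit for 6/20 is 0.519. Then 0.30 - √[(0.600 - 0.387)² + (0.519 - 0.300)²] = 0.30 - 0.306 = -0.006, a failure.

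**3. Exact power at the stated sizes.** Sum Bin(x; n, PT) × Bin(y; n, PC) over every pair (x, y) whose lower limit exceeds 0. Newcombe is taken without continuity correction.

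| | Normal approximation | Exact, Wald | Exact, Newcombe |
|---|---|---|---|
| Subgroup I, 28 per arm | 80.9% | 79.6% | 76.3% |
| Subgroup II, 20 per arm | 80.7% | 81.5% | 75.3% |

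A simulation of 200,000 trials agrees on the Newcombe figures (76.4% and 75.3%). The 80% therefore belongs to the Wald rule. With a continuity-corrected Newcombe interval, power would be 75.0% and 70.8%.

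**4. Allow for the saw-tooth.** Exact power moves unevenly with arm size. Subgroup I has 76.3% at 28/28 but 78.7% at 28/27 and 79.9% at 28/29. Subgroup II has 75.3% at 20/20 but 78.0% at 19/19 and 79.2% at 20/21. A fairer summary averages over the number of completers: sum Bin(m1; N, 0.85) × Bin(m2; N, 0.85) × power(m1, m2), with N = 33 or 24. This gives 77.9% and 77.3%.

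**5. Other reference points.**
- Smallest equal arms reaching 80% under Newcombe: 30 (80.2%) and 23 (81.9%).
- All 33 and 24 per arm evaluable: 86.0% and 84.4%.

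**6. Full analysis set with imputation (assumption: 15% missing in each arm, unrelated to response).**
- Missing counted as failure in both arms: rates become 0.85 × 75% = 63.75% v 0.85 × 40% = 34%, and 51% v 17%. Newcombe power at 33 and 24 per arm is 72.8% and 72.9%; Wald gives 72.8% and 75.2%.
- Missing imputed against the device: 63.75% v 34% + 15% = 49%, and 51% v 17% + 15% = 32%. Newcombe power is about 26% and 29%.

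**The case against.** The strongest reply is that nothing has been miscalculated and the gap is small. The protocol names its software, prints its formula and gets the sizes that the formula gives. Sizing by a normal approximation and then reporting a score-type interval is a choice of method. The headline gap of 4 to 5 points also depends on exactly 28/28 and 20/20; averaged over realistic completer numbers it is 2 to 3 points. The inputs are far less certain than that. The adult rate of 60% appears in the Introduction as 15/25, whose Wilson interval is 41% to 77%; over that range, Newcombe power at 20 per arm against a 20% control rate runs from 31% to 97%. Lowering the control rates from 40% to 38% and from 20% to 18% would bring power back to 80.8% and 80.5%.

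All of this stands, and it limits the weight of the point. It does not remove it: on the plan's own assumptions, power under its own rule is below 80% in both subgroups, at the stated sizes and on average.

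The dropout allowance is no answer either. The 86.0% and 84.4% need every randomised patient to be evaluable, whereas the plan adds those patients to offset the 15% it expects to lose.

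**Conclusion.** The point holds as a modest misstatement of power. Under the Newcombe rule, power per subgroup is 76.3% and 75.3% at exactly 28 and 20 evaluable per arm, and about 78% and 77% averaged over random dropout. This rests on the plan's response rates, a Newcombe interval without continuity correction and, for the averages, independent 15% dropout in each arm with completers analysed.

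Three stronger readings are not supported.
- A reader might infer an arithmetic error in the sample size. There is none; 28, 20, 33 and 24 all reproduce.
- A reader might conclude that the choice of interval lowers full-analysis-set power to about 73%. That loss comes mainly from the imputation, since the Wald rule falls to 72.8% and 75.2% under the same assumption. Section {20c} does not say what worst-case means, so 73% is one reading and 26% and 29% another.
- A reader might multiply the two subgroup powers and report a joint power. Whether both subgroups must succeed together is a separate question about the decision rule and says nothing about this mismatch.

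Nothing here biases the comparison or inflates type I error: upper-tail rejection under the Newcombe rule was 2.1% to 2.4% at common rates of 20%, 40% and 50%.

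**What to change.** Keep the sample size and the Newcombe rule. In Sample size {14}, replace the unqualified 80% with a statement that the sizes come from the printed normal-approximation formula, and that power under the Newcombe rule is about 75% to 78% per subgroup at the planned 15% dropout (86% and 84% if all 33 and 24 per arm are evaluable).

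Give power for the full analysis set only once section {20c} defines worst-case. Until then, give it as a range with the assumption stated: about 73% in each subgroup if missing counts as failure in both arms, and about 26% and 29% if missing is imputed against the device.

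The cost is wording and a slightly less favourable stated power. No extra patients or change of analysis are needed. Restoring 80% at equal arms would instead take 30 and 23 evaluable, hence 30/0.85, so 36, and 23/0.85, so 28 per arm: 128 patients rather than 114. A gap of this size does not require that. No interim analysis is planned and 43 of 114 patients were enrolled at the stated trial status, so the wording could be corrected before any outcome is analysed.

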### Objectives {7}

The objective of this clinical trial is to evaluate the efficacy and safety of the AR binocular treatment we developed. The primary objective is to compare the total effective proportion, defined as the proportion of patients with improvement of BCVA at distance in the AE no less than 0.2 logMAR, after 13 weeks of AR binocular training with that of traditional patching in patients with unilateral amblyopia. The secondary objectives of this study are (1) to compare the improvement in the visual functions at each follow-up visit between the two groups, including habitual-corrected visual acuity at distance, contrast sensitivity, near and far stereoacuity, and interocular suppression, (2) to compare the treatment adherence and adverse events between the two groups.

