### Methods for additional analyses (e.g., subgroup analyses) {20b}

The subgroups (aged 5 to < 18; ≥ 18) will be analyzed in both primary and secondary outcomes to test the consistency. The statistical methods follow the general principles of statistical analysis described above.

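### Superiority requires a positive interval in both age subgroups, but each subgroup is sized alone at 80% power and no power is given for meeting both; on the plan's own rates it is about 58 to 65%

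*Protocol article*

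**What the plan says.** **Decision rule (Analysis of primary endpoint).** The plan computes "the between-group difference in effective proportions (Newcombe 95% CIs) at 13 weeks within Subgroups I and II are calculated". It then attaches one conclusion to the two lower limits: if those for the "difference in effective proportions within Subgroups I and II are > 0, then superiority is established". A Cochran-Mantel-Haenszel analysis stratified by center follows, with no success criterion attached. No test pooled over age carries a decision.

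**Sizing (Sample size {14}).** The two age subgroups are planned one at a time, each "at the 5% significance level (two-sided) with 80% power". For Subgroup I (5 to under 18 years) "the sample size required for each group is 28, as calculated using the PASS 2022 software"; for Subgroup II (18 to under 55 years) "the sample size required for each group is 20 as calculated using the PASS 2022 software". Allowing for 15% dropout these become 33 and 24 per arm, and the sum over subgroups and arms is the 114 enrolled. No power is stated for the two subgroups jointly.

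**Role of the age groups elsewhere.** Under Methods for additional analyses {20b}, the same two age groups "will be analyzed in both primary and secondary outcomes to test the consistency".

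**The concern.** A rule that needs two independent tests to succeed is harder to meet than either test alone. With 80% power for each, the trial fails its own criterion more than a third of the time even when every planning assumption is true, and one small subgroup (20 evaluable patients per arm in adults) is enough to cause the failure. A reader who sees 80% beside both sample sizes has no way to learn this from the protocol.

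The wording under additional analyses adds to the difficulty. An age-group comparison that decides superiority cannot also be a check that some other primary result is consistent across age groups. As written, the protocol gives the same comparison both roles.

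**Working it through.** **Inputs, all from Sample size {14} and Analysis of primary endpoint.** Subgroup I: 75% against 40%, 28 evaluable per arm. Subgroup II: 60% against 20%, 20 evaluable per arm. Two-sided 5%, margin 0, 15% dropout. Interval: Newcombe 95%.

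**Step 1: reproduce the plan's sizes.** The printed formula is n = (1.96 + 0.8416)² x [Pc(1-Pc) + Pt(1-Pt)] / D².
- Subgroup I: 7.849 x (0.24 + 0.1875) / 0.35² = 27.39, rounded up to 28.
- Subgroup II: 7.849 x (0.16 + 0.24) / 0.40² = 19.62, rounded up to 20.
- Dropout: 28/0.85 = 32.9, so 33; 20/0.85 = 23.5, so 24; 2 x (33 + 24) = 114.

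Every stated size reproduces.

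**Step 2: power per subgroup by the same formula.** Power = Φ(D/SE - 1.96), with SE² = [Pc(1-Pc) + Pt(1-Pt)]/n.
- Subgroup I: SE = √(0.4275/28) = 0.1236; 0.35/0.1236 - 1.96 = 0.873; power 0.809.
- Subgroup II: SE = √(0.40/20) = 0.1414; 0.40/0.1414 - 1.96 = 0.868; power 0.807.

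**Step 3: power for the rule.** No patient is in both subgroups, so the two results are independent and the powers multiply.

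| Basis | Subgroup I | Subgroup II | Both |
|---|---|---|---|
| Nominal | 0.80 | 0.80 | 0.64 |
| Plan's formula, 28 and 20 per arm | 0.809 | 0.807 | 0.653 |
| Newcombe lower limit > 0, exact, 28 and 20 per arm | 0.763 | 0.753 | 0.575 |
| Newcombe, exact, 33 and 24 per arm, no dropout | 0.860 | 0.844 | 0.726 |
| Newcombe, exact, 33 and 24 per arm, 15% missing counted as failure in both arms | 0.728 | 0.729 | 0.531 |

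The exact rows sum the binomial probabilities of every outcome pair for which the Newcombe lower limit is above zero. The last row multiplies the response rates by 0.85, giving 63.75% against 34% in Subgroup I and 51% against 17% in Subgroup II.

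**Step 4: sensitivity to the meaning of worst-case.** The missing-data section {20c} names worst-case imputation without defining it. If it means failure in the training arm and success in the patching arm, the control rates become 49% and 32%, and the joint power is 0.256 x 0.285 = 0.073. The 53% figure is therefore conditional on an assumed definition.

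**Step 5: what 80% for the joint rule would need.** An equal split requires √0.80 = 0.894 in each subgroup. By the plan's formula that is 36 and 26 evaluable per arm, or 43 and 31 after dropout: 2 x 74 = 148 in total. By exact Newcombe enumeration it is 39 and 30, or 46 and 36 after dropout: 2 x 82 = 164.

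**The case against.** **The protocol never promises 80% for the trial as a whole.** This stands. The 80% is stated inside each subgroup and the sizes follow from it, so there is no arithmetic error. The gap is that the stated power and the stated success rule refer to different events.

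**The rule might mean a separate claim for each age group.** Sizing each age group as its own superiority comparison, because effects are expected to depend strongly on age, gives this some support. On that reading 80% per claim is right by the formula, and about 75 to 76% with the Newcombe interval. But the sentence joins the two subgroups with 'and' and draws one conclusion, so 'both' is the plain reading. If separate claims were intended, the sentence needs rewording.

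**A reader might infer that success in either subgroup suffices, and so that the false-positive rate is inflated.** The text does not support this: nothing in the protocol says 'either'. A rule requiring both needs no adjustment of the significance level; its only cost is power.

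**A reader might infer that the primary objective already calls for a test pooled over age,** since "The primary objective is to compare the total effective proportion". That is not established. The outcome section defines the proportion as responders over treated patients in each treatment group and does not say that 'total' means combined over age. The sample-size section uses the same term and then plans by age group.

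**A reader might take 53%, or even 7%, as the plan's own power.** Neither is. Both depend on how worst-case imputation is defined, which the article does not say.

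**Conclusion.** The point holds as a mismatch between the success rule and the power statement. If both intervals must exclude zero, the chance of success under the plan's own rates is about 64 to 65% by its formula and about 58% with the interval it will use. With complete follow-up of all 114 patients it is about 73%, still short of 80%. It falls to about 53% if 15% are missing and are counted as failures in both arms.

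These figures rest on the planned rates being true and on the plain 'both' reading. They do not show bias in the estimates or an inflated false-positive rate. The description of the same age groups as a consistency analysis is a separate, smaller inconsistency that should be resolved together with the rule.

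**What to change.** 1. **Sample size {14}:** state that 80% is the formula power within each subgroup, and that the power to meet the both-subgroups rule is about 64 to 65% by that formula and about 58% with the Newcombe interval. Any figure allowing for dropout should be given with the definition of worst-case imputation it assumes.
2. **Analysis of primary endpoint:** write that the lower limit must exceed zero in both Subgroup I and Subgroup II.
3. **Methods for additional analyses {20b}:** reword so that the age groups that carry the confirmatory decision on the primary outcome are not also presented as a consistency check of it.

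No extra patients are needed. The costs are a less favourable stated power and a protocol amendment while recruitment is under way (43 of 114 enrolled at the stated version), which needs a favourable opinion from the lead hospital if it counts as important. No interim analysis is planned.

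Two further routes are choices for the sponsor rather than corrections. One is to enlarge the trial for 80% joint power, to about 148 patients by the plan's formula or 164 by exact Newcombe. The other is to make one age-stratified pooled difference the confirmatory test, which by simulation has about 97% power at 28 and 20 per arm (about 95% at 33 and 24 with dropouts counted as failures). That gives up the requirement to show the effect in each age group: in simulation at the planned rates, the pooled test would still succeed about 64% of the time if the training worked only in Subgroup I, and a little over 40% of the time if it worked only in Subgroup II.
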